### Safety reporting

Due to the nature of ESRD and of HD, patients are likely to experience adverse events throughout the course of the study. Patients on HD have a large burden of co-morbid disease and, acute illness resulting in hospitalisations, new medical problems and deterioration of existing medical problems are expected throughout the study period.

All adverse events (AEs) or adverse reactions (ARs) and serious adverse events (SAEs) or serious adverse reactions (SARs) will be recorded from the time a patient enters the study to the final study visit. Each AE or AR will be considered for severity, causality and expectedness and may be reclassified as an SAE or SAR depending on the circumstances.

An SAE is any AE that:is life threateningrequires hospitalization or prolongation of a hospital admissionresults in a persistent or significant disability or incapacityis a congenital anomalyresults in death

All unexpected SAEs will be reported to the Glasgow Clinical Trials unit (CTU) within 7 days of awareness of the event, including a report assessing event intensity and likelihood of causality (see below) from the chief investigator or suitable nominated investigator. Study investigators will report all unexpected AEs, ARs, SAEs and SARs to the clinical trials unit, the sponsor, the Research Ethics Committee, and the Data Safety Management Board (DSMB).

Unexpected non-serious AEs will be assessed by the chief investigator, and should include an assessment of intensity and causality (see below), with reports being made within 14 days. These will be reported to the CTU and if appropriate to the sponsor, the Research Ethics Committee, and the DSMB.

The following guidance will be used to assess the intensity of an AE or an AR:Mild: The patient is aware of the event or symptom, but it can tolerate it easilyModerate: The patient experiences sufficient discomfort to interfere with or reduce his or her usual activitiesSevere: Functional levels are significantly impaired by the event such that patients can no longer carry out usual activities, or life is at risk from the event

The following guidance will be used to assess causality between an AE or AR and study participation:Unrelated: A causal relationship can definitely be excluded as another documented cause of the AE/AR is most plausibleUnlikely: A causal relationship is improbable and another documented cause of the AE/AR is most plausiblePossible: A causal relationship is clinically/biologically plausible and there is a plausible time sequence between AE/AR and study participationProbable: A causal relationship is clinically/biologically highly plausible and there is a plausible time sequence between onset of the AE/AR and study participation

### Data safety management board

The DSMB will be an independent group of experts, consisting a nephrologist, a cardiologist, lay member and a statistician, who will monitor patient safety and treatment efficacy data while the clinical trial is ongoing; the primary mandate of this committee is to protect patient safety. If adverse events of a particularly serious type are more common in the experimental arm compared to the control arm, then it would be within the remit of the DSMB to consider termination of the study if the risks outweigh the benefits for patients. All SAEs deemed to have a causal relationship with the intervention will be reviewed by the DSMB for individual consideration of patient safety and continuation within the trial.

#### Intervention fidelity and monitoring

Experience to date with our unit based exercise programme has shown this programme to work with very small dropout rates of <5 % and a number of studies of similar size with exercise interventions of 6–10 months report very good compliance (up to 99 %) with comparable dropout rates [71, 72]. Temporary noncompliance (e.g. intercurrent illness, holiday) will be allowed for by adding missed exercise sessions onto the end of the study period. Apart from the exercise intervention in the study group, usual care will be continued for both groups. The involvement of the nursing staff with the study will help aid compliance and monitoring and there will be frequent contact between patients and research staff.

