#### Follow-up assessments

Follow up visits are summarised in Fig. 1. A one-month run-in period allows the exercise group to familiarise themselves with intradialytic cycling. Three months after this run in period (four months from baseline), interim assessments will be conducted. This will involve all baseline assessments except the CMR, echocardiogram and NICOM. The control group will also undergo interim assessments at month four.

Final assessments will be conducted for both exercise and control groups after seven months. Assessments at study completion will be identical to the baseline visit.

Following study completion, patients will be offered the opportunity to continue with intradialytic cycling if they wish and control patients will be offered the chance to move to a shift where exercise intervention is available. We will also ask patients to complete a feedback and evaluation form for ongoing development of study and future service provision.

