#### Statistical analytic approach for primary outcome

The primary outcome is the change from baseline at six months in LV mass. Change from baseline will be calculated for each subject as the value at month six minus the baseline value. Differences in primary outcome measure between the intervention groups (exercise and control) will be tested within a linear mixed model containing a covariate for the intervention group and a random effect for the cohort (centre and shift). These models may be further adjusted for any imbalances between the intervention groups with respect to the baseline characteristics. All statistical analyses will be performed by a biostatistician from the Robertson Centre for Biostatistics, University of Glasgow.

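### Adding missed exercise sessions to the end of the study period conflicts with the common seven-month final assessment and could delay outcome measurement in the exercise arm only

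*Protocol article*

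**What the plan says.** All references are to the protocol article.

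- **Missed sessions (Intervention fidelity and monitoring).** Temporary non-compliance, with illness and holiday as the examples, "will be allowed for by adding missed exercise sessions onto the end of the study period". No cap is given, and no matching extension for controls. The same section says: "Apart from the exercise intervention in the study group, usual care will be continued for both groups".
- **Final visit (Follow-up assessments).** "Final assessments will be conducted for both exercise and control groups after seven months". On content: "Assessments at study completion will be identical to the baseline visit". Cardiac MRI is therefore part of it.
- **Interim visit (Follow-up assessments).** "Three months after this run in period (four months from baseline), interim assessments will be conducted". The article then limits what is done at that visit: "This will involve all baseline assessments except the CMR, echocardiogram and NICOM". The final scan is thus the only post-baseline cardiac MRI in the main trial.
- **Primary outcome (Statistical analytic approach for primary outcome).** "Change from baseline will be calculated for each subject as the value at month six minus the baseline value".
- **Event recording (Safety reporting).** Adverse events "will be recorded from the time a patient enters the study to the final study visit".

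**The concern.** Control patients have no exercise sessions to make up, so a rule that extends the study period for missed sessions can act in one arm only. It is also triggered by what happens after allocation. If the final visit moves with the study period, an exercise patient who falls ill is scanned after recovery and catch-up training, while nothing in the article extends follow-up for a comparable control. The arm contrast in left ventricular mass would then mix the effect of exercise with a difference in when, and in what state, patients are measured. An analysis plan cannot recover a scan that was taken at a different elapsed time.

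Safety is affected too. Event recording ends at the final visit, hospitalisations and deaths are listed as secondary outcomes, and the data safety management board may consider termination if serious events are more common in the exercise arm. Longer observation in that arm raises its crude counts even if exercise has no effect.

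A smaller matter of wording goes with this. The primary outcome is labelled month six, while the visit schedule counts the final visit as seven months.

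**Working it through.** **1. The schedule's own clock.** Run-in is one month and formal training six months (Intervention: intradialytic exercise training).

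- Interim visit: 1 + 3 = 4 months from baseline, as stated.
- Final visit: 1 + 6 = 7 months from baseline, as stated.

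The schedule is consistent with itself as long as no sessions are added. The abstract calls the month-four visit 3 months, so it counts from the end of run-in. On that clock the final visit is month six, which explains the label in the primary outcome. The change from baseline nevertheless spans about seven months, because baseline precedes run-in.

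**2. The two timing rules side by side.** One rule fixes the final assessments at seven months in both arms. The other extends the study period by the number of missed sessions, which is zero by definition for controls. Follow-up assessments describes the final assessments as those at study completion. If completion moves, they move, and the fixed seven months no longer holds in the exercise arm. If they do not move, the added sessions come after the outcome has been measured and cannot make up for non-compliance in it. The article does not say which is meant.

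**3. How far the visit could slide.**

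Inputs:
- Three sessions a week (article).
- Six months taken as 26 weeks.
- Seven months taken as 7 × 52/12 = 30.3 weeks.
- One session per dialysis day, so each added session costs one third of a week.
- The miss rate is an assumption. The article gives only a best case from similar studies, compliance of up to 99%, which corresponds to the 1% row.

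Formulas:
- Formal sessions = 26 × 3 = 78.
- Delay in weeks = 78 × miss rate / 3.
- Share of follow-up = delay / 30.3.

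| Assumed miss rate | Sessions added | Delay (weeks) | Share of seven months |
|---|---|---|---|
| 1% | 0.78 | 0.26 | 0.9% |
| 5% | 3.9 | 1.3 | 4.3% |
| 10% | 7.8 | 2.6 | 8.6% |
| 20% | 15.6 | 5.2 | 17.2% |

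These delays apply only if the final visit waits for the added sessions. With a constant event rate and comparison of crude counts, the last column is also the approximate excess in exercise-arm events with no effect of exercise.

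**4. What cannot be computed.** The article gives no rate at which left ventricular mass changes over time without exercise, so the delay cannot be converted into grams. The sample size of 65 per group does not depend on this point.

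**The case against.** The strongest reply is that postponement of the scan is inferred. The missed-session rule speaks of sessions, not of assessments, and the only section that sets assessment times gives seven months for both arms. This stands as a limit on the claim: a reader might infer that the article orders a later scan in the exercise arm, and it does not say so. It does not remove the conflict, because the two rules cannot both take effect on the outcome.

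A second reply is that visit windows, and rules for a control who is ill at month seven, may be in the full protocol, which is not shown. This also stands. The documents do not support saying that ill controls are always scanned on schedule, only that no extension is given for them.

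Third, compliance may be high and the effect on left ventricular mass small. If mass drifted by 1 g per month (an assumption), a 2.6-week mean delay would be worth about 2.6 / 4.345 × 1 = 0.6 g, or 4% of the 15 g target. This is a fair caution about the mean. However, Safety reporting expects acute illness and hospitalisation throughout the study, so the delays would be concentrated in the sicker patients, and elapsed time is only part of the problem.

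Fourth, clinical events may be analysed as rates under a statistical analysis plan that is not shown. That would deal with unequal exposure in the analysis, but not with the timing of the scan.

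Finally, a reader might infer from the month-six wording that the primary endpoint is never collected. The documents do not support this. The final visit includes cardiac MRI after six months of formal training, and as the only post-baseline scan it cannot be confused with another. The timeline figure, not shown, may settle the label.

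**Conclusion.** The article contains two timing rules that have to be reconciled: a common seven-month final assessment, and a one-arm extension for missed sessions. On the natural reading, the final cardiac MRI and the end of event recording would fall later in the exercise arm only, by an amount that depends on illness and absence after allocation. The delay is about 0.3 to 5.2 weeks for assumed miss rates of 1% to 20%, or about 1% to 17% of seven months. This rests on the final visit waiting for the added sessions and on the assumed rates.

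No bias in left ventricular mass of a given size or direction is shown, and none should be inferred. The point matters because it governs how the primary outcome is measured and should be settled before final scans are taken. The month-six label is a secondary matter: an inconsistent time origin, not a missing measurement.

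**What to change.** - In Intervention fidelity and monitoring and in Follow-up assessments, state that the final cardiac MRI and all other final assessments take place at the same elapsed time from baseline in both arms, regardless of sessions completed. The schedule's own seven months, with one common window, serves this purpose.
- Record missed sessions as adherence data. Whether make-up sessions continue after the assessment is for the investigators.
- Count clinical and adverse events to that common date, or compare them per unit of follow-up time.
- In the primary outcome definition, replace month six with the final visit (month seven from baseline).

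The cost is protocol wording, and that some exercise patients will be assessed with fewer sessions completed. The estimate then describes the programme as delivered over a fixed period. The sample size is unchanged.

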## Discussion

The primary aim of this study is to assess the effect of a six month programme of intradialytic exercise on LV mass as assessed by CMR. The cluster randomization design was chosen for the advantages in reducing exercise contamination of the control group and to ensure demographic homogeneity. There is the possibility that this could create selection bias if patients are aware which cohorts have been randomised to intervention and control before they are enrolled, but this will be minimised by not revealing the method of randomisation to patients until after they have consented to participation *and* completed all baseline assessments. This study will provide the opportunity to evaluate the effects of a structured programme of intradialytic exercise on a number of secondary outcomes. Whilst clinical outcome data will be collected, this study is not designed to evaluate the effects of exercise on mortality.

CMR used in this study is the gold standard technique for the quantification of LV mass, volumes and function. We anticipate it will be technically challenging to obtain high quality images for some patients who may struggle to lie flat for long periods or who find breath holding difficult. The CMR protocol has been carefully designed to acquire all desired images in the most efficient way possible and have pioneered techniques that allow shorter scan times, with the primary outcome measure obtained early in case of premature scan termination. The CMR radiographers at the NIHR-Leicester Cardiovascular BRU have many years’ experience obtaining scans from patients with similar burdens of co-morbid disease [45, 76, 77]. The increased signal noise ratio obtained at 3 T allows the faster acquisition of cine images (4–5 s) for patients who are poor at breath-holding and free-breathing techniques can also be used with acceptable image quality.

There are some data suggesting interdialytic exercise may yield superior cardio-respiratory adaptations to intradialytic exercise programmes, but with significantly higher drop-out rates [18, 19]. Given the proven benefits of intradialytic exercise programmes compared to control patients and the superior adherence rates [18], pragmatically an intradialytic exercise programme was chosen as it is the most likely to be translated successfully into clinical practice.

The adoption of intradialytic exercise programmes into clinical practice has been slow and this has, in part, been attributed to patient and clinician concerns regarding safety [78–82]. The study is designed so that interim analysis will provide data on the arrhythmogenic potential of intradialytic exercise. This should in turn help to alleviate patient and staff concerns regarding the safety of exercise on dialysis.

## Conclusion

This study will test the hypothesis that an intradialytic programme of exercise leads to a regression in left ventricular mass, an important non-traditional cardiovascular risk factor in end stage renal disease. We will also evaluate the efficacy, feasibility and safety of an intradialytic exercise programme using a number of secondary end-points. We anticipate that a positive outcome will lead to both an increased patient uptake into established intradialytic programmes and the development of new programmes nationally and internationally.

## Abbreviations

ACSM, American College of Sports and Exercise Medicine; BCM, body composition monitor; BIS, bioimpedence spectroscopy; CMR, Cardiac Magnetic Resonance Imaging; CVD, cardiovascular disease; DSMB, data safety management board; ECHO, echocardiogram; eCRF, electronic case report form; EQ-5D-5L, Euro Qol-5 Dimension-5 Levels; HD, haemodialysis; LV, left ventricular; LVEF, left ventricular ejection fraction; LVH, left ventricular hypertrophy; MRI, magnetic resonance imaging; NICOM, non-invasive cardiac output monitoring; NIHR, National Institute for Health Research; RCT, randomised-controlled trial; RPE, rating of perceived exercise; SCD, sudden cardiac death; SD, standard deviation; SF-12, short form-12 questionnaire
